#### 2.2.1. Collecting Packs from Tobacco Retailers

The data collection team will determine a central point (such as a bus station, a government building, or a market place) in each PSU. All types of shops, such as tea stalls, kiosks, supermarkets, department stores, and cigarette shops that sell cigarettes or birri, or both, would be eligible to take part in the study. Enumerators will walk half a kilometer in both directions on the main street around the public gathering place and approach all the retailers meeting the eligibility criteria. All eligible retailers will be provided with both verbal and written information about the study. If they agree to take part, they will be required to sign the consent form. Following consent, the field worker will proceed to pack collection. The retailers would be supplied with a “collection bag” on the previous day and asked to keep all the empty packs resulted from loose sale on the following day since the shop opened in that bag. All “collection bags” will be retrieved by the field workers at the end of the business day. We will provide a small monetary reward of BDT 3 (GBP 0.03) per empty pack deposited in the collection bag. In case the empty pack of the cheapest and popular brands were not available in the bag from a particular retailer, the team would take a picture and code all the relevant attributes of such pack observed in the shop itself [3]. 

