#### 2.2.2. Collecting Discarded Packs from Streets

In addition to collecting empty packs from the tobacco retailers, discarded packs from the streets where those retailers are established and also from some other locally important streets around public gathering places will be accumulated [3]. The distance that would be covered in each street would be one kilometer (half a kilometer in each direction). The field workers would use separate “collection bag” with unique identification number for collecting the discarded packs in each area. The pack collection from streets would take place simultaneously during the day when the “collection bag” to the retailers would be distributed. The street selection would also consider the street condition for walking and possibility of finding littered packs. Necessary safety equipment such as masks and gloves will be provided to the field staff while collecting littered packs. 

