#### 2.2.5. Field Design and Implementation

Ten data collectors will be recruited and attend a one-day training session on: (a) getting packs from retailers; (b) getting packs from the streets; and (c) collecting packs from trash recycle market. The in-house training will focus on the ways of finding the public gathering places, selecting the retailers, instructing the retailers about pack preservation for the day maintaining certain qualities, and collecting the packs. They will also receive training on obtaining informed and written consent, how to generate the “Unique ID” for the “Collection Bags”, how the packs should be preserved, and how to collect discarded packs from the streets. The data collection would be carried out during the period February 2020 to September 2020 and the analyses be performed by March 2021.

The Research Fellow and one field supervisor will visit the study sites during data collection period to check the survey is done properly. They will also visit a subset of the chosen retailers. Data will be monitored for quality and completeness by the core research team. Due to the sensitive nature of the research study, we will make our best efforts to provide security measures to our data collectors. We will group the data collectors together, whenever possible. We will prescribe specific hours for data collection, outside of which data collectors will not be allowed to collect data. Every data collector will have a cell phone with pre-paid credit and a dedicated team member will be on-call during the prescribed data collection time, to provide assistance regarding the questions or any issue in the field. 

All the collection bags will be brought back to the research office where we will have data entry operators to inspect the packs and register their characteristics into the database for further analysis. The training for data entry operators will take place with the direct support from National Board of Revenue (NBR) officials in Bangladesh. The relevant officials will be invited to share the techniques and expertise they employ when they examine the authenticity of tax stamps on cigarettes. 

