## 3. Analysis Plan

We will classify a cigarette pack as illicit if it has at least one of the following attributes: No mention of “retail price”: It is mandatory to print the retail price of the goods “on the body of the goods or on every package, sachets or cells distinctly, conspicuously and indelibly”. This applies to cigarettes, and packs not containing the retail price can be considered illegal [21].Mention of brand element: Packets should not contain any brand elements, for instance Light, Mild, Low Tar, Extra, and Ultra. Packs mentioning brand element will be considered illegal [22].No graphic health warnings: Health warnings shall be printed on both sides of the packet covering at least 50% of the total area of each main display area. In addition, the warnings should be in colored pictures. Rules notified further suggests that the ratio and written warnings should be 6:1 and the written warnings has to be printed in black background with white font color. Packs not fully complying the above rules will be considered illegal [21,22].No textual health warnings: The following warnings should be printed on the packet in Bengali, otherwise it can be considered as illegal [21,22].
(a)Smoking causes throat and lung cancer;(b)Smoking causes respiratory problems;(c)Smoking causes stroke;(d)Smoking causes heart disease;(e)Second-hand smoke causes harms to the fetus;(f)Smoking causes harms to the fetus; or(g)Second-hand smoking causes death.No declaration: Selling of tobacco products without having the statement “Sales allowed only in Bangladesh” printed on the packets would be illegal [22].A duty-free sign: Cigarette packs collected from retailers with a “duty-free” sign will be classified as illegal as these are to be sold in Duty Free shops only and should not be available in the market.Absence of correct and authentic tax stamp/banderole: The government has made it obligatory to use tax stamp or banderole on cigarette packets. Any sale of cigarette without this tax stamp or banderole is legally prohibited. The banderole/stamp of cigarette pack of different size and design had been defined [21]. We will check if the packs have used banderole/stamp correctly as per the SRO and VAT Booklet, and if the banderole/stamp is genuine.

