The packs collected from different sources would be kept in separate bags and analyzed separately. In addition, the features of the respective packs would be recorded in three different databases to find separate estimates of illicit cigarettes. The estimates from first two inter-related methods will be triangulated and hence complementing each other. We will then compare and validate these findings with the third method. Given the availability of the trash market in the study sites, and adequate volume of packs collected from the trash market, the findings will be compared with the first two methods. We will assess the extent to which the result of trash market measure corresponds to first two measures to estimate of illicit trade for its validity. Findings from pack analysis would be further triangulated with the retailer interview findings for better understanding of the pattern of illicit practices in the cigarette market. 

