Another important potential limitation of the proposed methodology would be its ability of correct estimation for the size of illicit market. Since the unit of observation from where packs would be collected is retail cigarette shops, selection bias might remain present in the estimation. The estimate would be overestimated if pack collection takes place in an area where illegal tobacco products are known to be traded. In contrast, the estimates would be underestimated if retailers purposefully preserve the licit cigarette packs in the collection bag. Moreover, conditioning that illicit cigarettes are sold in full packs in general rather than single sticks, collecting empty packs from retailers might underestimate the magnitude. Considering all these potential threats, we expect the study would be free from selection bias as the retailer selection would be completely random covering the urban–rural and border–non-border perspective around the country. The validity and representativeness of the estimate measured using the packs collected from retailers would be ensured by comparing that with the estimate retrieved from littered packs from the streets and packs collected from the trash recycle market in the same neighborhood. Estimates from the two later sources to a greater extent would address the limitations if retailer deposit only licit packs or illegal cigarette happens to be sold in full pack. The comparison of results and further analysis of illicit packs from these three sources would help us to examine the existence of any systematic difference among them. Absence of systematic difference would ensure the possible unbiasedness of the estimates [12].

Finally, in the absence of any prevalence data at the division or district level, it would not be possible to propose a sample size weighted on the local smoking prevalence or smoking intensity. Bangladesh has completed two rounds of Global Adult Tobacco Survey (GATS). However, the first round does not have district level or divisional level information on smoking prevalence while the data from second round have not been released yet. 

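### Operators know each pack's source when they judge it, because packs are bagged and recorded separately by source, and agreement between sources is then used as evidence of validity

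*Protocol article*

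**What the plan says.** Section 2.2.5 (Field Design and Implementation) brings all collection bags to the research office, where there will be "data entry operators to inspect the packs and register their characteristics into the database for further analysis". Revenue officials support the operators' training. Section 3 (Analysis Plan) then states that "The packs collected from different sources would be kept in separate bags and analyzed separately", and that "the features of the respective packs would be recorded in three different databases to find separate estimates of illicit cigarettes". Section 2.2.2 gives the street collection a "separate “collection bag” with unique identification number for collecting the discarded packs in each area".

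The label follows a fixed rule: "We will classify a cigarette pack as illicit if it has at least one of the following attributes". Among the attributes, operators must decide whether the stamp was used correctly and "if the banderole/stamp is genuine", and whether the graphic warning meets an area rule (50%) and a ratio rule (6:1). Section 4 (Discussion) adds that packs whose stamp is not in a state to be checked are left out of the study.

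One group of packs is not coded at the office. Where a retailer's bag lacks the cheapest and popular brands, Section 2.2.1 says that "the team would take a picture and code all the relevant attributes of such pack observed in the shop itself".

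The Analysis Plan judges the trash-market method by how well its result corresponds to the retailer and street results. The Discussion says that comparing the three sources will help to "examine the existence of any systematic difference among them", and treats finding none as assurance that the estimates may be unbiased.

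**The concern.** The factor being compared, the pack source, is visible to the person who records the outcome. For a printed price or a duty-free sign this hardly matters. For the authenticity of a stamp or the dimensions of a warning it can, and under the any-one-attribute rule a single strict or lenient call decides an otherwise compliant pack.

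The clearest route is the missing stamp. The Analysis Plan makes a pack without a stamp illicit, while the Discussion excludes a pack whose stamp cannot be checked, having noted that stamps may come off when packs are opened or littered. An operator who knows that a pack came from the street or the trash market may put a missing stamp down to littering and exclude the pack. The same pack from a retailer's bag may be read as never stamped and counted as illicit.

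At stake are research question (c), which is a comparison of sources, and the support that the comparison lends to the retailer estimate in question (a). If coding leans on source, a difference may be an artefact, and agreement may be one too.

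**Working it through.** The plan gives no figure on this point, so there is nothing to reproduce. The check has two parts.

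**1. Is source known when judgement is used?**

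- Who inspects and who enters: the same operators (Section 2.2.5).
- How packs are held: in separate bags by source (Section 3).
- Where data go: one database per source (Section 3). Section 2.2.5 speaks of a single database, so the two sections need to be reconciled. On the Analysis Plan's wording, an operator must know the source to know where to enter the pack.
- Items that are mainly presence or absence: retail price, brand words, textual warning, declaration, duty-free sign.
- Items that need judgement: stamp genuineness and correct use, warning area and ratio, and the choice between illicit and excluded when a stamp is missing or damaged.
- Use of the result: correspondence between sources (Section 3) and absence of systematic difference (Section 4).

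So source is known for the judgement items, and the source comparison rests on them.

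**2. How large could an artefact be?** All coding rates below are assumptions.

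*Borderline packs.* Let b be the share of packs that are borderline on a judgement item and otherwise compliant, and q1 and q2 the proportions of them called illicit in two sources. With identical packs, the spurious difference is b × (q1 − q2). With q1 = 0.60 and q2 = 0.40:

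- b = 2%: 0.02 × 0.20 = 0.4 percentage points
- b = 5%: 0.05 × 0.20 = 1.0 point
- b = 10%: 0.10 × 0.20 = 2.0 points

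*Missing stamps, called illicit or excluded.* If the borderline share b consists of packs without a checkable stamp, those not called illicit leave the denominator. With no other illicit packs, the estimate is bq / (1 − b + bq). For b = 5% this is 3/98 = 3.06% at q = 0.60 and 2/97 = 2.06% at q = 0.40, again a difference of 1.0 point.

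*Difference in false-positive rate.* With the same true illicit share p in both sources, and a false-positive rate 1 point higher in one, the difference is (1 − p) × 0.01. The values of p below are those cited in the Introduction:

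- p = 2% (the figure derived from industry estimates): 0.98 points, 49% of the true share
- p = 11.6% (global): 0.88 points, 8% of the true share
- p = 16.8% (low- and middle-income countries): 0.83 points, 5% of the true share

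*Hiding a difference.* True shares of 2% and 4% would look equal if the lower source had a false-positive rate of (0.04 − 0.02) / 0.98 = 2.0% with no missed packs, or if only 0.02 / 0.04 = 50% of illicit packs were detected in the higher source with no false positives.

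**The case against.** The strongest reply is that the room for discretion is small. The rule is fixed, most attributes can be read off the pack, and the 50% and 6:1 criteria are measurable. Operators are trained with revenue officials, stamps are checked against official specifications, a standard pack analysis tool exists, and the core team monitors data quality. This stands as far as it goes: it confines the point to the stamp, the warning dimensions and the exclusion decision. None of it hides the source.

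A second reply is that an article leaves coding procedure to a manual, which may provide for second reading. That is fair, and the absence of such detail is not the criticism. The criticism is of what the article does state: a fuller manual could mask source only by departing from the separate bags and databases.

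Third, the numbers return their inputs. This also stands. A pack that fails another attribute is illicit either way, so the borderline illustration covers only otherwise compliant packs. Nor is 2% clearly the right yardstick, because the study's definition counts any listed packaging breach.

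A reader might infer more than the text supports:

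- That operators see border status or post code. Bags carry unique identifiers, but the documents do not say what these encode.
- That inspection goes bag by bag, tying operator drift to site. The order of reading is not stated.
- That operators expect more illicit packs from certain places. Nothing describes their expectations.
- That a formal test is at risk. The plan describes comparison and correspondence, with no test specified.
- That a coding artefact could never be detected. The packs are brought to the office, and nothing says they are discarded before a second reading could be made.

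**Conclusion.** The point holds for knowledge of source. As stated, the workflow reveals the source to the person making a few consequential judgements, and agreement between sources is then read as support for validity. Source-aware coding could create or hide a difference. The documents do not show that it does, and they give no rates from which to estimate its size.

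On the stated assumptions (2% to 10% borderline packs, called illicit 60% versus 40% of the time), the artefact is 0.4 to 2.0 percentage points, with 1.0 point at 5%. In relative terms this matters most if illicit packs are rare. It does not invalidate the design. It is a weakness in the source comparison that can be reduced cheaply because inspection is already central.

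**What to change.** At the research office:

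1. Give each pack a neutral code on receipt that shows neither source nor site.
2. Inspect in batches mixed across sources and post codes.
3. Make the stamp-exclusion decision under the same masking, with one written rule for when a missing or damaged stamp means illicit and when it means excluded.
4. Have operators record attributes in one database. Lock the coding, then merge the source and site key. Rules that depend on source, such as the treatment of duty-free packs and its adjustment, are applied after the merge.
5. Obtain the separate estimates from a source variable, and report exclusions by source.
6. Flag packs coded in the shop (Section 2.2.1) as unmasked, and show the source comparisons with and without them.
7. State that masking is partial, since street and trash packs may look worn.
8. Align Sections 2.2.5 and 3 on the number of databases.

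The cost is modest handling time per pack for relabelling and mixing. No extra field work is needed, and the separate estimates that the Analysis Plan wants are kept.

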## 4. Discussion

Over the last two and half decades, several significant advances have been made on studying illicit tobacco trade. This body of evidence has identified the following three key themes of particular relevance for research on illicit tobacco trade: (1) different ways to measure illicit tobacco trade; (2) distortion of the data by tobacco industry; and (3) effectiveness of interventions to address the problem of illicit trade [23]. 

The empirical estimation of the extent of illicit trade in the tobacco market often remains an intricate and challenging task. Tobacco control researchers around the world often triangulate several methods to improve the precision of their estimates of the magnitude of illicit trade [24]. The volume of scientific literature is skewed towards the high- and upper middle-income countries [1,4,5,6,7,17,25,26,27,28,29,30,31,32,33,34] relative to the low- and lower middle-income countries [11,24,35,36,37,38]. This is perhaps due to the issue of data availability and research capacity. Compared to LMICs, a greater potential loss in government revenue due to illicit trade in high-income countries, owing to higher tax rates, results in a higher public investment on related research. On the other hand, the dimension of illicit trade in LMICs is different [1]. Although the extent of financial incentive would be lower for illicit tobacco traders in those countries, the risks associated with such malicious activities would also be lower due to lack of governance, which might encourage the illicit traders to extend their activities there. Therefore, the importance of research in illicit trade in Bangladesh cannot be ignored. 

In addition, existing works prescribed to follow country specific approach towards illicit trade as uniform ranking of research priorities within the arena appears to be impossible [1,34]. Taking into account the country context, this attempt would be a considerable contribution to the field of illicit tobacco trade research in Bangladesh.

This study is being conducted as part of a research consortium of fifteen partner organizations across eight countries (Bangladesh, Ethiopia, Ghana, India, South Africa, the Gambia, Uganda, and the UK) funded by the Global Challenges Research Fund in the UK and named the “Tobacco Control Capacity Programme” [39]. We have established a national stakeholders’ group in Bangladesh and arranged several stakeholder engagement meetings to get their feedback on the study protocol. 

The successful implementation of the protocol is subject to endorsed inspection of collected packs and data recording about the authenticity of tax stamp. According to the local tobacco control laws, a tax paid pack must contain the tax stamp and we are in need of examining the security features of the tax stamp for study purpose. In practice, in most cases, these tax stamps are affixed in the upper left- or right-hand corner in the outer part of a cigarette pack. Thus, it might happen that the required tax stamp is removed, lost, or torn while opening by the retailers or littering by the smokers into the streets and trash bins. Considering this potential threat, the gold standard would have been collecting the unopened packs for tax and other compliance inspection [12]. This scope is limited in the current context due to the fund challenge that has to be made with respect to the sampling design. Hence, training on eligibility criterion for an empty cigarette pack to be included in the inspection basket would be of sheer importance. All the packs where tax stamps are not in proper status to be checked for authenticity would be excluded from the study. 

Another important potential limitation of the proposed methodology would be its ability of correct estimation for the size of illicit market. Since the unit of observation from where packs would be collected is retail cigarette shops, selection bias might remain present in the estimation. The estimate would be overestimated if pack collection takes place in an area where illegal tobacco products are known to be traded. In contrast, the estimates would be underestimated if retailers purposefully preserve the licit cigarette packs in the collection bag. Moreover, conditioning that illicit cigarettes are sold in full packs in general rather than single sticks, collecting empty packs from retailers might underestimate the magnitude. Considering all these potential threats, we expect the study would be free from selection bias as the retailer selection would be completely random covering the urban–rural and border–non-border perspective around the country. The validity and representativeness of the estimate measured using the packs collected from retailers would be ensured by comparing that with the estimate retrieved from littered packs from the streets and packs collected from the trash recycle market in the same neighborhood. Estimates from the two later sources to a greater extent would address the limitations if retailer deposit only licit packs or illegal cigarette happens to be sold in full pack. The comparison of results and further analysis of illicit packs from these three sources would help us to examine the existence of any systematic difference among them. Absence of systematic difference would ensure the possible unbiasedness of the estimates [12].

Finally, in the absence of any prevalence data at the division or district level, it would not be possible to propose a sample size weighted on the local smoking prevalence or smoking intensity. Bangladesh has completed two rounds of Global Adult Tobacco Survey (GATS). However, the first round does not have district level or divisional level information on smoking prevalence while the data from second round have not been released yet. 

Contemplating the context of Bangladesh, the data challenges along with the data quality required in other methods increases the suitability of observational analysis. In addition, it would help researchers and in turn policy makers to learn about the pattern of illicit activities related to packaging compliance and initiate the proper policy measure henceforth. In addition, the estimate along with analysis would help us to enhance our knowledge regarding how an important stakeholder in supply chain (retailers) is legally used to reach to the smokers. 

